### Study design

This study is designed as a multi-center, prospective, observational, open cohort study. Initiation of recruitment has been staggered across sites, with the earliest commencing in February 2019 and additional sites beginning recruitment in 2021. Enrollment is scheduled to complete in December 2022, with follow-up to complete in June 2023. In total, approximately 2476 patients are expected to be enrolled in the study. Patients will be followed to collect key clinical and treatment-related data including overall survival and QOL metrics until death or loss to follow up. QOL metrics will be assessed at the time of study enrollment, prior to the initiation of treatment, and during post-treatment follow up (1 month after initiation of treatment, 3 months after initiation of treatment, and then every 3 months until death or loss to follow up). The accrual period is expected to range between 22 and 47 months across sites. Duration of follow up will differ by site due to the staggered initiation of recruitment, however, study participants will be followed for at least 6 months and up to a total of 53 months.

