### Sample size

We aim to recruit all patients with ESCC based on histological confirmation or presumptive clinical diagnosis that meet the eligibility criteria at participating AfrECC sites. We forecast a total accrual of an estimated 2476 study participants across all six sites (see Table 1) over the duration of the study. This estimate is based on annual ESCC cases observed in recent case series at KCH (unpublished data), annual recruitment to a recent case-control study at KCMC [18], as well as annual accrual rates in the present study at ORCI, MNH, and Tenwek since study initiation (Tenwek Hospital, *n* = 220 study participants per year; ORCI, *n* = 130 per year; and MNH, *n* = 150 per year). Of the total study population, we estimate 1102 study participants will be treated with esophageal stenting, 145 with chemotherapy, 464 with radiotherapy, 212 with concurrent chemoradiation, 450 with supportive care alone, and 103 with esophagectomy. Based upon previous data that indicate median OS following stenting is 36 weeks [10], radiotherapy with or without chemotherapy is 27 weeks [13, 19], and chemotherapy is 14 weeks [5, 19], our primary analysis comparing OS of different palliative interventions for ESCC will have the following power to detect differences between each pairwise comparisons based upon alpha of 0.0167 (adjusting for 3 comparisons based on Bonferroni correction): stenting vs. radiotherapy with or without chemotherapy, power = 0.99; stenting vs. chemotherapy, power = 1.00; and radiotherapy with or without chemotherapy vs. chemotherapy, power = 1.00.

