Cochran-Armitage test will be used to compare symptom metrics assessed using the ‘Modified Rosenblatt Index’ (Dysphagia, Odynophagia, ‘Chest and/or Back pain,’ WHO performance status, and ‘Overall Well-being’ since starting treatment) between each of the different palliative EC treatments (chemotherapy, radiotherapy, chemoradiation, esophageal stenting, basic supportive care) at each time point: 1 month after initiation of treatment, 3 months after the initiation of treatment and then every 3 months thereafter. We will also test for within-subject differences in scores between baseline (or pre-treatment) and each of post-treatment time points by McNemar’s Chi-squared test. In addition, generalized estimating equations (GEE) framework will be applied to analyze this longitudinal QOL data, where the treatment will be considered as the fixed effect and the subject-specific effects are the random effects.

Complications will be summarized as number of patients (%) with 95% confidence intervals and compared between treatment arms by Chi-squared test. Among palliative interventions, secondary outcome measures related to dysphagia will be compared using log-rank test and cph models to adjust covariates, including age, sex and baseline clinical covariates. ‘Time to achieve any dysphagia relief’ will be defined as time from treatment to improvement in dysphagia score of greater than or equal to 1. ‘Duration of dysphagia relief’ will be defined as time elapsed after treatment with any improvement in dysphagia from baseline. ‘Dysphagia-adjusted survival’ will be defined as the total time period with a dysphagia score of 0 to 2.

Measures of healthcare utilization and process measures related to the delivery of ESCC treatment by treatment approach will be examined as exploratory endpoints. Time-to-event measures will be compared among treatment groups by log-rank test. Count of hospitalization events, and total number of days hospitalized during and after ESCC treatment will be compared among treatment groups by ANOVA (or Kruskal Wallis test when normality assumption is not held). Chi-squared test will be used to compare the need for subsequent intervention for recurrent or persistent dysphagia by treatment approach. All analyses will be performed overall and within each site.

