Palliative interventions for EC have been an active area of research over the last several decades. Most of this research has taken place in HICs, with several RCTs having investigated best practices for palliation among patients with either ESCC or esophageal adenocarcinoma [9]. These studies highlight the tradeoffs between esophageal stenting with SEMS and the use of radiation-based therapies in patients with advanced disease [22, 23]. SEMS have been shown to provide immediate dysphagia relief, but are prone to failure over time due to stent migration and/or recurrent obstruction. Radiation-based therapies, including external beam therapy (EBRT) with or without chemotherapy and brachytherapy, have delayed effects, but may offer more durable symptom control. Steyerberg et al. developed and validated a prognostic index to help guide treatment selection in this patient population, with the rationale that SEMS may be advantageous for those with short life expectancies [24]. Subsequent efforts to evaluate this index in a South African patient population found that it had poor predictive value in this context, highlighting the challenges of generalizing evidence from clinical trials in HICs to low resource settings [25]. Advanced dysphagia, severe weight loss, and malnutrition are all much more prevalent among patients with EC in these settings. Access to supportive care is often more limited as well. These differences, both in terms of patient characteristics and health system factors, underscore the importance of advancing research on treatment strategies for ESCC in sub-Saharan Africa, with the goal of optimizing treatment delivery in this context. Although RCTs remain the gold standard in comparative effectiveness research, several challenges emerge with this study design in Eastern Africa, including the ethics of randomizing patients who are often in poor general condition, and the time, infrastructure and resources needed for implementing well-designed clinical trials [26, 27].

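### As written, the longitudinal QOL model has a treatment effect but no visit term, so a symptom time course shared by all treatments can appear as a treatment difference, mainly in chemotherapy contrasts

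*Protocol article*

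**What the plan says.** Under Statistical methods, the protocol article says that a "generalized estimating equations (GEE) framework will be applied to analyze this longitudinal QOL data". The same sentence goes on to describe the terms of that model as one "where the treatment will be considered as the fixed effect and the subject-specific effects are the random effects". No visit, time, treatment-by-time, baseline-score or covariate term is given for this model there or elsewhere. The Cox models for the dysphagia outcomes, in the next paragraph, do name adjustment covariates.

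The GEE is additional to two other sets of QOL analyses in the same paragraph. Cochran-Armitage tests compare treatments at each visit ("1 month after initiation of treatment, 3 months after the initiation of treatment and then every 3 months thereafter"), and McNemar tests compare baseline or pre-treatment scores with each later visit within patients.

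Study design sets the number of scores per patient: assessments at months 1 and 3, "then every 3 months until death or loss to follow up". It also states that "study participants will be followed for at least 6 months and up to a total of 53 months". Sample size gives the planning survival: "median OS following stenting is 36 weeks", with 27 weeks for radiotherapy with or without chemotherapy and 14 weeks for chemotherapy.

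**The concern.** A model with treatment and subject effects alone compares each group's scores averaged over whatever visits that group supplied. Groups with shorter survival supply mostly early scores; groups with longer survival supply more late ones. If symptoms change over time in the same way under every treatment, those averages differ although the treatments do not differ at any visit.

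The direction of the error depends on which rows are used. Higher scores are worse. With follow-up rows only and shared worsening, the longest-surviving group (stenting) looks worst. With baseline rows included and a shared early improvement, the shortest-surviving group (chemotherapy) looks worst, because untreated baseline scores form a larger part of its data. The GEE sentence does not say whether baseline rows enter.

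The protocol itself expects symptoms to move with time. Its Discussions section describes stent relief as prompt but liable to fail later, and says that radiation-based therapies "have delayed effects, but may offer more durable symptom control". One averaged coefficient cannot show that contrast.

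QOL is a named secondary endpoint, and the article presents QOL by treatment as one of the study's main contributions.

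**Working it through.** **Inputs.** From Sample size: medians of 36, 27 and 14 weeks; groups of 1102 (stenting), 464 + 212 = 676 (radiotherapy with or without chemotherapy) and 145 (chemotherapy). From Study design: visits at months 1, 3, 6, 9, ... and follow-up of 6 to 53 months. Assumed: exponential survival, 4.345 weeks per month, censoring uniform on 6 to 53 months, no loss to follow-up.

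**The plan's own figure.** The protocol gives no power or effect size for QOL. Its OS power checks that the inputs are read as intended. For stenting versus radiotherapy, HR = 36/27 = 1.333. With about 1452 events, group fractions 0.62 and 0.38, and two-sided alpha 0.0167, power = Φ(√(1452 × 0.62 × 0.38) × ln 1.333 − 2.394) = Φ(5.32 − 2.39) = 0.998. The plan states 0.99, so the inputs are consistent.

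**Step 1: visit mix.** The probability of a score at month v is S(v) × C(v). Here S(v) = 2^(−4.345 v / median); C(v) = 1 up to month 6 and (53 − v)/47 after it.

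| | Stenting | RT ± chemo | Chemo |
|---|---|---|---|
| Alive at month 1 | 0.92 | 0.89 | 0.81 |
| Alive at month 3 | 0.78 | 0.72 | 0.52 |
| Follow-up rows per patient | 3.83 | 3.12 | 1.87 |
| Share of rows at month 1 | 24% | 29% | 43% |
| Share at month 6 or later | 56% | 48% | 29% |
| Mean assessment month | 8.07 | 6.59 | 3.81 |
| Baseline share, if one baseline row is used | 21% | 24% | 35% |

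Simulated cohorts gave 55%, 49% and 29% at month 6 or later.

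**Step 2: expected spurious difference.** Under working independence and a linear shared trend, the treatment-only coefficient converges to the trend times the difference in mean assessment month. For a shared worsening of 0.2 point per 3 months (0.0667 per month):

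- stenting minus chemotherapy: 0.0667 × (8.07 − 3.81) = 0.28 point
- stenting minus radiotherapy: 0.0667 × (8.07 − 6.59) = 0.10 point

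These are for an unbounded score. Exchangeable correlation reduces them: a run of 60 cohorts gave about 0.17 and 0.06.

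For a shared 1-point improvement after baseline and flat scores afterwards, with one baseline row included, the chemotherapy-minus-stenting difference is the gap in baseline shares: 0.349 − 0.207 = 0.14 point. With follow-up rows only, it is zero.

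**Step 3: false-positive rate.** There were 400 simulated cohorts per scenario, with a 0-4 score, within-subject correlation 0.5, linear GEE with robust standard errors, exchangeable working correlation, nominal 0.05, and no treatment difference at any visit. The trends are assumptions.

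| Shared trend | Stent v RT | Stent v chemo | RT v chemo |
|---|---|---|---|
| Worsening 0.1 per 3 months, follow-up rows | 11% | 20% | 12% |
| Worsening 0.2 | 27% | 54% | 26% |
| Worsening 0.3 | 49% | 83% | 42% |
| 1-point relief, no drift, baseline row included | 16% | 47% | 27% |

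With baseline included and relief followed by drift of 0.1 to 0.2, the two biases nearly cancel and rates are 5-14%. Working independence gives higher rates in the follow-up-only drift scenarios. Adding visit as a categorical term gives 3-7% in every scenario.

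**Step 4: sensitivity.** Two rough runs of 60 cohorts each separated radiotherapy alone (464) from chemoradiation (212). At 0.005 (0.05 over the ten pairs among five QOL groups), drifts of 0.1, 0.2 and 0.3 gave about 0, 3 and 15% for stenting versus radiotherapy, and 5, 15 and 48% for stenting versus chemotherapy. With an assumed 10% per month loss to follow-up, rates at 0.05 were 3, 3 and 8%, and 7, 25 and 18%. The last series is not monotone, which shows the simulation noise.

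**The case against.** The strongest reply is that the sentence only sorts effects into fixed and random and was never meant as a full list of regressors. A journal article condenses, and a SAP that is not shown could add visit. This stands in part: a reader might infer that treatment is definitely the only fixed effect, and the text does not say so. But it does describe the model, calls treatment the fixed effect, and is silent on time where the neighbouring Cox models name their covariates. An analyst who follows it as written gets the biased model.

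A reader might also infer that the whole QOL comparison is unsound, or that this is the only use of the repeated scores. The documents do not support either. The per-visit Cochran-Armitage tests compare treatments within a visit, so visit mix cannot affect them. Time to relief, duration of relief and dysphagia-adjusted survival also use the repeated dysphagia scores and do not pass through this model. These analyses also address early against durable relief. They do not correct the GEE, and a spurious GEE result would sit beside them unexplained.

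The objections to the size are sound. The trends are assumed. The simulation pools radiotherapy with chemoradiation and omits supportive care (450 patients), for which no survival figure is given. The main table ignores Bonferroni correction and loss to follow-up, so its top figures are upper-end values.

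**Conclusion.** The concern holds in a limited form. Followed literally, the GEE credits a shared time course, or a differing share of baseline rows, to treatment. The imbalance in visit mix follows from the protocol's own medians and schedule, given exponential survival. It is large for chemotherapy against stenting (29% against about 55% of follow-up rows at month 6 or later) and modest for radiotherapy against stenting (about 49% against 55%).

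The size of the bias cannot be fixed from the document. It runs from nil (flat post-treatment scores, no baseline rows) to the upper-end rates in the working, and it falls with multiplicity correction or loss to follow-up. The defect is confined to one model for a secondary endpoint. It is worth correcting because a wrong QOL ranking of treatments is possible and the remedy is nearly free.

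**What to change.** State the GEE mean model as treatment, visit as a categorical factor (months 1, 3, 6, 9, ...) and treatment-by-visit, fitted to post-treatment scores. Report between-treatment contrasts at named visits, for example months 1 and 3, in place of one averaged treatment coefficient. If an unseen SAP already includes visit, align this sentence with it.

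The cost is one sentence, a few more parameters and no new data. Late chemotherapy contrasts will be imprecise: 145 × 2^(−4.345 × 6/14) = 145 × 0.275, or about 40 patients expected alive at month 6.

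A visit term removes the visit-mix problem but not truncation by death. Late contrasts should be described as comparisons among patients still alive and reached. Under the planning medians this caveat already matters at month 3, when about 52% of the chemotherapy group would be alive against 78% of the stenting group.

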**Overall well-being** Which of the following best describes your quality of life now as compared to before you were treated for esophageal cancer?	“A lot better”	“A little better”	“The same”	“A little worse”	“A lot worse”

^a^Modified quality of life index reprinted with permission from Rosenblatt (2010, Table 1)

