#### Patient interviews

Interviews with study participants will be conducted at the following specified time-points: (i) at time of study enrollment); (ii) prior to the initiation of treatment (within 4 weeks); and (iii) during post-treatment follow up (1 month after initiation of treatment, 3 months after initiation of treatment, and then every 3 months until death or loss to follow up). Research assistants will collect data on sociodemographic characteristics, medical history, and baseline QOL through face-to-face administration of oral questionnaires at the time of study enrollment. QOL assessments are based on the ‘Modified Rosenblatt Index,’ [16] a questionnaire comprised of six patient-reported outcomes assessing for the presence and severity of the following as scored on a Likert scale: Odynophagia, Dysphagia, ‘Chest and/or Back pain,’ WHO performance status, and ‘Overall Well-being’ since starting treatment (see Table 2). Subsequent interviews assessing vital status and QOL will be performed through mobile phone outreach. During post-treatment follow up, research assistants will attempt to contact patients a minimum of three times over the follow up interval before patients are classified as “lost to follow up.” Outreach attempts will be made at varying times of the day on three different days of the week.

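### The planned quality-of-life analysis is wrong as written in four places: a GEE given random effects, McNemar's test on 3-to-5-level scores, a change item compared with baseline, and an analysis list that omits one of six items

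*Protocol article*

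**What the plan says.** The protocol article's Statistical methods section plans three analyses of the Modified Rosenblatt Index.

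- **Between treatments, at each visit:** "Cochran-Armitage test will be used to compare symptom metrics". The items listed for this are "Dysphagia, Odynophagia, ‘Chest and/or Back pain,’ WHO performance status, and ‘Overall Well-being’ since starting treatment".
- **Within patients:** the plan is to "test for within-subject differences in scores between baseline (or pre-treatment) and each of post-treatment time points by McNemar’s Chi-squared test". No cut-point is given.
- **Longitudinal:** a GEE, specified as one "where the treatment will be considered as the fixed effect and the subject-specific effects are the random effects". No other model term is named.

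The instrument is set out in Table 2 (Secondary endpoints). It has six items: Dysphagia, Odynophagia, Regurgitation, Chest-back pain, WHO performance status and Overall well-being. The last one asks: "Which of the following best describes your quality of life now as compared to before you were treated for esophageal cancer". Patient interviews calls the index "a questionnaire comprised of six patient-reported outcomes" and then names five. Table 3 schedules the whole index at baseline, before treatment and at follow-up.

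**The concern.** These are methods the article states, not details it leaves out. Followed literally, the longitudinal model cannot be specified, the paired test needs an unstated dichotomy, one item is compared with a baseline value that has no meaning, and one collected item falls outside the list.

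Quality of life is a secondary endpoint. The Discussion nevertheless presents the study as the first in sub-Saharan Africa to evaluate quality-of-life benefit by treatment. If the model and the cut-point are settled after the data are seen, both become post hoc choices, and the direction of a within-patient result can depend on the cut.

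Treatment is also not randomised, and it is tied to site. In Table 1, one Tanzanian centre offers external beam radiotherapy but no stents, while one Kenyan centre offers stents but no radiotherapy. A quality-of-life model whose only named term is treatment would therefore mix treatment with case mix.

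**Working it through.** **1. GEE against random effects.** In a GEE, dependence within a patient enters through a working correlation, and the coefficient is population-averaged. In a mixed model it enters through a subject random effect, and the coefficient is conditional on the subject. For categorical outcomes the two differ. As an illustration, take a dichotomised item with an assumed conditional odds ratio of 0.50 and average over a normal random intercept:

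| Random-intercept SD (assumed) | Marginal odds ratio |
|---|---|
| 0.5 | 0.52 |
| 1 | 0.56 |
| 1.5 | 0.61 |
| 2 | 0.66 |
| 3 | 0.73 |

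The models also differ under missing data. An unweighted GEE generally needs data missing completely at random; a likelihood-based mixed model needs only missing at random.

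**2. McNemar against the scale.** The levels in Table 2 are Dysphagia 5, Odynophagia 4, Regurgitation 4, Chest-back pain 3, WHO performance status 5 and Overall well-being 5. An item with k levels has k − 1 possible cuts, so 4, 3, 3, 2, 4 and 4. None is chosen.

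An invented paired table of 200 patients on a 5-level score shows why this matters. The cells, baseline to follow-up, are: 4→3, 20; 4→4, 5; 3→2, 60; 3→3, 60; 2→2, 20; 2→3, 10; 1→2, 15; 1→1, 10. McNemar's statistic is (improved − worsened)² / (improved + worsened).

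- Cut at 2 or more: 0 improve and 15 worsen, so 15²/15 = 15.0 (p ≈ 0.0001, worsening).
- Cut at 3 or more: 60 improve and 10 worsen, so 50²/70 = 35.7 (p < 0.0001, improvement).

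Power is not the main reason to change. Assume a baseline mix of 3/10/27/45/15% over scores 0 to 4, with 35% improving one level, 20% worsening one level, and the cut at 3 or more. Simulation with 2,000 replicates gives uncorrected McNemar 0.52 against signed-rank 0.56 at n = 76, and 0.81 against 0.83 at n = 145.

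**3. Overall well-being.** The item compares now with before treatment. A patient not yet treated has nothing to compare. A previously treated patient, who is eligible under Eligibility criteria, would answer about a different treatment. Neither answer is a baseline for the post-treatment score.

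**4. Item count.** Table 2 has six items, and Patient interviews says six. The lists under Secondary endpoints, in footnote c of Table 3, under Patient interviews and under Statistical methods each have five. Regurgitation is the missing item in all four.

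**5. Who is left to compare.** Sample size gives median survivals of 36 weeks (stenting), 27 weeks (radiotherapy with or without chemotherapy) and 14 weeks (chemotherapy). With exponential survival, the fraction dead at t is 1 − 0.5^(t/median). Take 3 months as 13.04 weeks:

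- Stenting: 1 − 0.5^(13.04/36) = 0.222, or 22%.
- Radiotherapy with or without chemotherapy: 1 − 0.5^(13.04/27) = 0.285 (0.2846 before rounding), or 28%.
- Chemotherapy: 1 − 0.5^(13.04/14) = 0.476, or 48%.

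The 3-month comparison is therefore made on quite different surviving fractions.

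**The case against.** The article is condensed, and much of this could be settled in a fuller document. Some stronger readings go further than the text allows.

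- **That quality of life will be analysed without baseline or covariate adjustment.** The article names treatment as the fixed effect but does not say it is the only one. Baseline enters the within-patient test, the dysphagia time-to-event outcomes are adjusted for age, sex and clinical characteristics at baseline, and every analysis is repeated within site. This part rests partly on silence, so it belongs in the fix and is not an error in itself.
- **That the McNemar analysis cannot be run, or loses much power.** Extensions to k × k tables exist (Bowker, Stuart-Maxwell), and the power gap for the uncorrected test is small. What stands is that neither an extension nor a cut is stated.
- **That Cochran-Armitage is the wrong test.** It suits a two-group comparison of an ordinal score; its limit is that it is unadjusted.
- **That Regurgitation will never be analysed.** The GEE sentence refers to the longitudinal data as a whole, and the short list may be a copied omission. The contradiction in the count remains.
- **That death is ignored.** Dysphagia-adjusted survival combines survival with swallowing. It does not cover the other items. The survivor fractions show that deaths are unequal; they do not show bias in any particular estimate.

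No statistical analysis plan excuses the four stated points. A plan that repeated this wording would inherit the same faults.

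**Conclusion.** The point holds for four statements: random effects in a GEE, a paired binary test on ordinal scores with no cut, a baseline comparison for a change item, and five listed items against six. These follow from the text alone. They should be fixed, but they are confined to a secondary endpoint. Overall survival, its power, the sample size and data collection do not change.

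The odds-ratio table, the 200-patient example and the power figures are illustrations on assumed inputs, and they predict nothing about this cohort. The 3-month death fractions of 22%, 28% and 48% rest on the plan's medians, exponential survival, and survival counted from the start of treatment. They are reason enough to label visit-by-visit results as applying to survivors.

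**What to change.** 1. **Model.** Choose one: an ordinal GEE with a working correlation and robust standard errors, dropping the random-effects wording, or an ordinal mixed model with a subject random intercept. Include treatment, time, treatment × time, the baseline item score, and the covariates already planned for the dysphagia time-to-event outcomes.
2. **Within-patient test.** Replace McNemar with Wilcoxon signed-rank or Stuart-Maxwell. The reason is fit to the scale and avoiding a post hoc cut.
3. **Overall well-being.** Leave it out of the baseline comparison and use no baseline score for it in the model. Test post-treatment answers against the category *The same*.
4. **Items.** Add Regurgitation to the analysed items and correct the four five-item lists.
5. **Death.** Describe per-visit comparisons as among survivors, and add a sensitivity summary with death as the worst category. A random-intercept model does not by itself deal with truncation by death.

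The cost is wording only. Item scores, covariates and vital status are all collected already under Tables 2 and 3. The changes should be fixed before the quality-of-life data are analysed.
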